# Parenteral nutrition during neoadjuvant chemotherapy for patients with non-metastatic gastric or esophago-gastric cancer to reduce postoperative morbidity (PERCOG): study protocol for a randomized controlled trial

**DOI:** 10.1186/s13063-017-2388-3

**Published:** 2017-12-28

**Keywords:** Gastric cancer, Cancer of the esophago-gastric junction, Neoadjuvant chemotherapy, Parenteral nutrition, Postoperative complications, Comprehensive Complication Index, Randomized controlled trial

## Abstract

**Background:**

The majority of patients with gastric or esophago-gastric cancer are at risk for malnutrition. Preoperative malnutrition was shown to increase the incidence of postoperative complications following abdominal surgery. However, it remains unclear if preoperative parenteral nutritional support during neoadjuvant chemotherapy (NACT) may be effective to reduce the rate of postoperative complications in these patients.

**Methods/Design:**

The PERCOG trial is a randomized controlled multicenter observer-blinded trial, investigating if the improvement of the general condition of patients with non-metastasized gastric cancer or cancer of the esophago-gastric junction during NACT by supplemental parenteral nutrition can decrease the postoperative Comprehensive Complication Index (CCI). Statistical analysis of the primary endpoint measure (CCI on postoperative day 30) will be based on the intention-to-treat population. The global level of significance is set at 5% and the sample size (n = 150) is determined to assure a power of 80%.

**Discussion:**

The results of the PERCOG trial will provide high-level evidence for clinical recommendations regarding the administration of preoperative supportive parenteral nutrition and provide all participating patients the opportunity of an improved treatment.

**Trial registration:**

German Clinical Trials Register, DRKS00009451. Registered on 3 July 2017.

**Electronic supplementary material:**

The online version of this article (doi:10.1186/s13063-017-2388-3) contains supplementary material, which is available to authorized users.

## Background

### Rationale

Malnutrition affects the majority of surgical oncological patients and negatively influences the postoperative outcome. In particular, patients with cancer of the upper gastrointestinal tract (GIT) have an increased risk for malnutrition-associated, postoperative complications. Malnutrition weakens the immune system, which in turn increases the risk for infections and impaired wound healing. In addition, postoperative hypermetabolism leads to an increased energy and protein demand, which can result in or contribute to malnutrition of these vulnerable patients [1]. In patients with adenocarcinoma of the stomach or the esophago-gastric junction staged cT2 cN+ cM0 up to cT4 cN+ cM0, neoadjuvant chemotherapy (NACT) followed by the oncological resection of the tumor is the standard therapy concept in Germany [2]. The PERCOG trial aims to resolve the question if supportive parenteral nutrition during the NACT of these patients can decrease the incidence of postoperative complications following the oncological tumor resection. Reporting of postoperative complications in surgical trials is often non-standardized and thus results are difficult to assess and compare between trials. Therefore, the chosen primary endpoint of the PECOG trial is the Comprehensive Complication Index (CCI), which includes all types of postoperative complications independent of their severity and has been shown to be more sensitive than other existing morbidity endpoint [3–5].

### Previous trials

Several studies previously investigated the effect of preoperative nutritional interventions on the postoperative outcome after abdominal surgery. However, their results are not unequivocal. A multicenter cohort study of 512 patients showed that preoperative supportive nutrition significantly reduced the risk of postoperative complications after abdominal surgery in patients at risk for malnutrition (Nutritional Risk Score [NRS 2002] ≥ 5) [6]. In these patients, the preoperative nutrition intervention also significantly reduced the length of postoperative hospital stay [7]. Many other studies did include only small patient numbers and/or showed methodological flaws and/or did not investigate clinically relevant endpoints. In a meta-analysis of 13 randomized controlled trials (RCTs), preoperative parenteral nutrition reduced the rate of postoperative complications about 10% [8]. However, the included trials differed substantially in included indications, operations, and endpoints. In another meta-analysis of 26 RCTs, it was shown that preoperative lipid-free parenteral nutrition reduced the rate of postoperative complications in malnourished patients [9]. However, the definitions of malnutrition in the included studies varied largely. A systematic review and meta-analysis of the Cochrane Group also showed that preoperative parenteral nutrition of malnourished patients reduced the risk for severe postoperative complications [10]. Significantly, only three RCTs were included in this meta-analysis, since all other trials failed to fulfil the required quality of reporting. Finally, another systematic review of 41 trials (including non-RCTs) did not support these results. Even if a slightly reduced rate of postoperative complications was observed in the group of patients receiving preoperative parenteral nutrition, it failed to achieve statistical significance [11]. In addition, several studies investigated the question, which surgical patients could especially benefit from preoperative nutritional support. Results from two older trials suggest that patients with malignancies of the upper GIT could especially benefit from preoperative nutritional support [12, 13]. These results were confirmed by a more recent RCT, in which the subgroup of patients with malignancies of the GIT showed the most significant effect of the preoperative nutritional support [14].

In conclusion, the existing evidence implies that preoperative parenteral nutrition can reduce the rate of postoperative complications after surgery for malignancies of the upper GIT. This group of patients is exposed to an increased risk of malnutrition because of the reduced food intake due to the anatomical location of the tumor, as well as nausea and loss of appetite, which are frequently caused by the NACT. Therefore, many of these patients experience clinically relevant loss of weight during NACT.

### Objective

This multicenter clinical RCT aims to improve the general condition of patients with non-metastasized gastric cancer or cancer of the esophago-gastric junction during NACT by supportive parenteral nutrition, in order to decrease the postoperative CCI [5]. The results of the PERCOG trial will provide high-level evidence for clinical recommendations regarding the use of preoperative supplemental parenteral nutrition and provide all participating patients the opportunity of an improved treatment.

## Methods/Design

### Trial sites

The PERCOG trial will be conducted in at least four surgical departments (university hospitals), all of which are members of the German surgical trial network (CHIR-*Net*) and have previously participated in multicenter trials within this network. All of the study personnel involved in the trial require training according to the International Conference on Harmonisation of Technical Requirements for Registration of Pharmaceuticals for Human Use – Good Clinical Practice (ICH-GCP) and will be specifically instructed in all trial-specific procedures before initiation of the trial, conforming to German Drug Law (*Arzneimittelgesetz*– AMG [15]) and GCP regulations [16]. After training by the principal investigator, the local home care service will administer the parenteral nutrition to patients according to their standard procedures.

### Trial population and eligibility criteria

All adult patients (aged > 18 years) with histologically confirmed adenocarcinoma of the stomach or the esophago-gastric junction staged cT2 cN+ cM0 up to cT4 cN+ cM0 will be eligible if they are able to understand the extent and nature of the PERCOG trial and provide written informed consent to participate.

Exclusion criteria were defined as: (1) non-resectable primary tumor, judged by the treating surgeon; (2) pregnant or breast-feeding women; (3) Eastern Cooperative Oncology Group (ECOG) score > 2; (4) NRS < 3; (5) insufficient liver, kidney, or bone marrow function, judged by the treating oncologist; (6) manifest cardiac illness (unstable coronary artery disease, heart failure New York Heart Association [NYHA] class IV) or respiratory illness (chronic obstructive pulmonary disease [COPD] class IV) that represent a contraindication either for the NACT or the surgical resection of the tumor; (7) participation in another interventional clinical trial that interferes with the primary or secondary outcomes of this trial; and (8) insufficient patient compliance.

### Sample size

A total of 150 patients have to be recruited (for calculation, see “Statistical methods”), 75 patients per group.

### Type of trial

This is an observer-blinded, multicenter, superiority surgical RCT with two parallel study groups, phase III-b according to German Drug Law (*AMG*).

### Recruitment and trial timeline

Only specialized oncological surgical centers with the required infrastructure will be included in the trial to achieve the target sample size. The recruitment period is set to 27 months (first patient in to last patient out 32 months). Figure 1 shows the trial flow scheme and Fig. 2 (SPIRIT figure) the schedule of enrolment, interventions, and assessments according to the SPIRIT 2013 statement [17]. The SPIRIT checklist for the study protocol can be found in Additional file 1.

**Fig. 1 Fig1:**
[figure not shown]
*Flowchart* of the PERCOG trial. CCI Comprehensive Complication Index, neoadj. neoadjuvant, Ctx chemotherapy, GEJ gastro-esophageal junction

**Fig. 2 Fig2:**
[figure not shown]
SPIRIT figure for the PERCOG trial

### Randomization and blinding

Before inclusion in the trial, a GCP-certified investigator will perform the screening and detailed information of patients and will obtain their written informed consent. A member of the study team will perform randomization after completion of study visit 1. An online tool of the Munich Center of Clinical Trials (*Münchner Studien Zentrum* [MSZ]) will be used to generate the allocation sequence. This online tool uses pre-defined randomization lists, which will be created block-wise at the Institute of Medical Statistics and Epidemiology of the TUM. Basic characteristics of the patient and day of randomization must be documented on the printed randomization sheets. Subsequently, randomization sheets must be stored away from the patient records and trial documents to assure blinding. To ensure observer blinding, the assessment of primary and secondary outcomes will be performed by medical doctors, which are not otherwise integrated in the conduct of the trial and blinded to the group allocation of participants. Observers will be surgeons of spatially separated participating study centers, specifically trained in the assessment of the CCI. The observer training has to be documented on a separate training log. The observers will receive the patient’s surgical file only. Before sending the file, it has to be verified that this file contains data on the postoperative treatment only and no data that allow conclusions about the pre-surgical supportive treatment. All patient-related data and data concerning the study intervention have to be blanked out. The oncological file, in which the study specific treatment is documented, will not be available to the independent observers. To ensure blinding, the observers will not perform patient visits but assess the CCI on basis of the surgical file only. Blinding of patients is not feasible. Unblinding of the local principal investigator is permissible if significant hazards for individuals’ safety or welfare occur.

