In addition, the following outcome measures have been defined as secondary endpoint measures: (1) rate of serious adverse events (SAEs) and adverse events (AEs) during NACT according to the Common Terminology Criteria for Adverse Events (CTCAE v4.03.); (2) rate of AEs/SAEs associated with the administration of parenteral nutrition according to CTCAE v4.03; (3) morbidity and mortality within 30 days postoperatively according to the Calvien Dindo classification (Table 1) [19]; (4) quality of life (QoL) according to the results of EORTC (European Organization for Research and Treatment of Cancer) QLQ-C30 questionnaire; (5) change of weight and body mass index (BMI); (6) length of postoperative hospital stay; and (7) length of postoperative ICU say.

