### Safety evaluation and reporting of adverse events

All AEs/SAEs from the moment of randomization until the last study visit have to be assessed, documented, and reported by the local clinical investigator or designated sub-investigator. Postoperative complications and surgical complications do not have to be documented as AE/SAE, but will be documented according to the Clavien Dindo Classification (visits 7–9). During preoperative chemotherapy (visits 2–5), changes of laboratory parameters that are expected because of the underlying illness and that are graded < 3 according to CTCAE v4.03 do not have to be reported as AEs.

SAEs have to be reported within 24 h and will be classified by intensity, outcome, and causality. Exceptions are: (1) hospital treatment planned before inclusion in the study; (2) planned admission to the hospital for NACT; and (3) hospital admissions because of the underlying disease as long as they are not because of an aggravation of the disease.

All SAEs will be subject to a second assessment by a designated person who will be independent from the reporting investigator and the trial sponsor. According to AMG and GCP regulations, the ethics committee and the competent federal health authority will be informed of all suspected unexpected serious adverse reactions (SUSARs) and all SAEs resulting in death or being life-threatening. Safety reports resuming all AE/SAEs have to be compiled regularly by the principal investigator to reassess the risk–benefit analysis.

If a female participant gets pregnant during the trial, the investigator has to report the pregnancy to the sponsor within 24 h after becoming aware of it. It is recommended to follow-up on the pregnancy and outcome.

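### The claim that blinded outside observers assess the secondary outcomes does not hold for adverse events, weight and BMI, or quality of life

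*Protocol article*

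**What the plan says.** **Who assesses.** Randomization and blinding states, with no exception, that "the assessment of primary and secondary outcomes will be performed by medical doctors, which are not otherwise integrated in the conduct of the trial". These doctors are surgeons from other participating centers, blinded to group.

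**What they see and do.** The same section says "The observers will receive the patient’s surgical file only". It requires a check that "this file contains data on the postoperative treatment only and no data that allow conclusions about the pre-surgical supportive treatment", and adds that "The oncological file, in which the study specific treatment is documented, will not be available to the independent observers". It closes the description with "the observers will not perform patient visits but assess the CCI on basis of the surgical file only". Data collection and management brings in independent observers once, at visit 9, for the primary endpoint.

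**What the secondary outcomes are.** Outcome measures lists seven. The first is the "rate of serious adverse events (SAEs) and adverse events (AEs) during NACT" and the second the "rate of AEs/SAEs associated with the administration of parenteral nutrition according to CTCAE v4.03". Endpoint 3 is 30-day Clavien Dindo morbidity and mortality, 4 is QLQ-C30, 5 is change in weight and BMI, and 6 and 7 are lengths of hospital and ICU stay.

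**Who assesses adverse events.** Under Safety evaluation and reporting of adverse events, all AEs and SAEs from randomization to the last visit "have to be assessed, documented, and reported by the local clinical investigator or designated sub-investigator". SAEs then receive a second assessment by someone independent of the reporting investigator and the sponsor.

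**The concern.** The article calls the trial observer-blinded and extends that protection to every secondary outcome. Its own procedures withhold from the observers the material needed for several of those outcomes and give the adverse-event work to someone else. Both statements cannot be true for endpoints 1 and 2.

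These endpoints are where the trial checks the harms of parenteral nutrition during chemotherapy. The Risks section accepts a slightly higher risk of port infection as outweighed by the expected benefit, and Safety analysis plans chi-square or Fisher's exact tests of AEs and SAEs between groups. CTCAE grading, and above all attribution to parenteral nutrition, involve judgement that knowledge of the arm can influence. A final report that followed the blinding section would present these comparisons as blinded when they were not. Open-label recording of adverse events is ordinary and often unavoidable; the fault is in claiming otherwise.

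**Working it through.** No figure in the plan bears on this point, so the check is a comparison of sections, endpoint by endpoint.

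**Endpoint 1 (AEs/SAEs during chemotherapy).** The events occur before surgery. Data collection and management has them assessed at the visits during chemotherapy. The observers' file is confined to postoperative treatment, the oncological file is withheld, and they see no patients, so they have nothing from which to assess this endpoint. The safety section names the local investigator or sub-investigator instead. It also exempts postoperative and surgical complications from AE/SAE documentation, so most of the AE/SAE data lie outside what the observers receive.

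**Endpoint 2 (AEs/SAEs linked to parenteral nutrition).** The same reasoning applies. In addition, linking an event to parenteral nutrition requires knowing that it was given, which is exactly what the redaction removes. No blinded assessment is possible.

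**Endpoint 5 (weight and BMI).** Anthropometric data are taken at baseline and at visits 4 and 5, all before surgery. The observers cannot supply them.

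**Endpoint 4 (QLQ-C30).** The patient is the assessor, and the blinding section itself says that patients cannot be blinded.

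**Endpoint 3 (Clavien Dindo).** This can be scored from the postoperative file, so blinded assessment is feasible, although the article does not say outright that the observers do it.

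**Endpoints 6 and 7 (lengths of stay).** These are postoperative durations that a surgical file could contain. The conclusion does not rest on them.

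Count: the claim fails for endpoints 1, 2, 4 and 5, four of seven.

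**Could the local assessors be blinded themselves?** Two statements point that way: randomization sheets are kept apart from patient records, and unblinding of the local principal investigator is allowed for safety reasons. Against this, Data collection and management has the planned route and product of parenteral nutrition recorded for experimental patients at visit 3, and has the NRS 2002 repeated at visit 4 in controls only. Whoever completes or reads these visit records can tell the arm. In any case, a local investigator takes part in running the trial, so the description of the assessors in "the assessment of primary and secondary outcomes will be performed by medical doctors, which are not otherwise integrated in the conduct of the trial" is not met.

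**Does the second SAE assessment repair it?** That person is described as independent, not as blinded, and covers SAEs only. Non-serious AEs, which are part of both endpoints, get no such review.

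**Primary analysis.** The sample size rests on a CCI difference of 10 points with a standard deviation of 20. No safety or other secondary endpoint enters it, so resolving the contradiction changes neither the 150 patients nor the 80% power.

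**Illustration only.** The article gives no AE rate and no measure of recording bias. Assume that 50% of patients in each arm have a given type of AE, with 75 per arm and no true difference, and that knowledge of the arm lowers recording in one arm by a relative fraction d. The apparent difference is 0.50 × d, with SE = √(0.50 × 0.50/75 + p₂(1 − p₂)/75) and p₂ = 0.50(1 − d).

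| d | p₂ | Difference | SE | Difference/SE | Chance of two-sided p < 0.05 |
|---|---|---|---|---|---|
| 5% | 0.475 | 0.025 | 0.082 | 0.31 | 6.1% |
| 10% | 0.450 | 0.050 | 0.081 | 0.61 | 9.4% |
| 15% | 0.425 | 0.075 | 0.081 | 0.92 | 15.2% |

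These rows show how such a bias would act. They do not estimate it, and the point stands without them.

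**The case against.** The strongest reply is that the article corrects itself. The sentences after the broad claim confine the observers to the surgical file and the CCI, and the visit 9 description names them for the primary endpoint only. On that reading one sentence is too wide, in a condensed article, and no site would be misled about who does what. This largely stands as to practice. It does not rescue the claim, which is unqualified and is the statement a later report would cite.

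Several other replies stand and limit the point:

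- Analysis of secondary endpoint measures makes these endpoints descriptive and any testing exploratory, so no confirmatory conclusion depends on them.
- For endpoint 2 the issue is a claim that could never be true, rather than a safeguard that was omitted. Controls normally receive no parenteral nutrition, so a bias argument about the between-arm comparison has little content there.
- Weight and BMI are measurements and leave less room for judgement than CTCAE grading.
- Parenteral nutrition is given by the home care service or qualified nurses, and the article implies some intended local blinding. The article therefore makes it likely, but does not say outright, that every adverse-event assessor knows the arm.

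A reader might go further and infer that the harms comparison is biased by a known amount, or that the primary endpoint has lost its blinding. The documents support neither. They contain no event rate or recording difference, and this contradiction leaves the observers' scoring of the CCI from the redacted file as described.

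**Conclusion.** The concern holds as an internal contradiction about a stated bias safeguard. Observer blinding as claimed under Randomization and blinding is absent for secondary endpoints 1 and 2, and also for preoperative weight and BMI and for QLQ-C30. The conclusion rests on the article's text alone: the limits on the observers' file and task, the assignment of AEs and SAEs to the local investigator, and the visit at which each outcome is recorded. It needs no assumption about rates. The schedule figure is not available here.

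The consequence is moderate. It concerns how the safety and other secondary results may be described, including the between-group AE/SAE tests. It does not touch the CCI analysis, the sample size or the power. The correction is worth making because it is specific and nearly free.

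**What to change.** 1. In Randomization and blinding, limit the blinded-assessment claim to outcomes scored from the redacted surgical file: the CCI and, if so intended, 30-day Clavien Dindo morbidity and mortality.
2. State that endpoints 1, 2, 4 and 5 are assessed without observer blinding.
3. Reconcile the sentence on unblinding the local principal investigator with Data collection and management and with the safety section, so that it is clear whether any local assessor is meant to be blinded and to what.
4. Report the AE/SAE comparisons under Safety analysis as open-label.

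The cost is a few sentences: no extra patients, visits or staff, and no change to the primary analysis. The stated blinding becomes narrower, which is the accurate description. Having the second SAE assessor grade from narratives with the arm removed would be an optional addition. It would be a new procedure, would cover SAEs only, and could not work for events attributed to parenteral nutrition, so it is not part of the required change.
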